#### Analysis of primary and secondary study outcomes

Outcome measures will need to demonstrate internal consistency with Kenyan youths as indexed by a Cronbach’s alpha of at least 0.70 [50] to be considered for further analyses.

Our analyses will follow an intent-to-treat approach, including all participants initially randomized to an intervention condition. We will run a linear mixed-effects model comparing intervention and control groups on each primary and secondary outcome. Models will be organized to reflect the hierarchical structure of the data described earlier with crossed random effects for schools and group leaders and strict hierarchical nesting for observations in participants, participants in groups, and groups in group leaders. All models will include a random intercept that will allow for individual variation at baseline. We will include a random slope that will allow for individual variation in outcome change rates; however, should this result in overfitting (i.e., random effects structure becoming too complex to be supported by the data), we will remove the random slope to allow for more parsimonious models. Time, intervention condition, and their interaction will be included in all models. Covariates will include age (in years) and sex. Age will be included because older adolescents are reported to face increased psychosocial stress, which may exacerbate depressive and anxiety symptoms [25, 51]. Sex will be included because sex differences in internalizing problems have been documented in Kenyan adolescents [24, 25, 29, 52]. We will build two models, one which will include schools a random slope thus allowing for variation in outcome change rates by school, and another with school as a covariate because students in resource-poor schools in Kenya have reported higher anxiety symptoms than students in schools with more resources [25]. We will use Akaike Information Criterion (AIC) to determine which of the two models will be a better fit for the data. Significant (*p* < .05) condition × time interactions in predicted directions will indicate that the intervention condition produced more rapid improvements in outcomes across the full study period (baseline to 4-week endpoint), as compared to the control.

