We will calculate effect sizes (ESs) for total pre- to post-intervention change in depressive symptoms (the primary study outcome) using differences in means; these ESs will compare mean gain scores (Cohen’s *d*) reflecting changes in each outcome from baseline to post-treatment for youths in the Shamiri intervention versus study skills control intervention. Statistically significant, positive Cohen’s *d* values will indicate greater improvements for intervention group youths versus control group youths.

Participants who miss one or more intervention sessions will be permitted to attend future sessions. Missing data will be imputed as described earlier. As part of our main analyses, we do not plan to carry out additional analyses such as subgroup analyses to gauge for intervention effects on primary and secondary outcomes. However, we may later conduct additional exploratory analyses (e.g., moderator analyses) in papers separate from those reporting main and secondary trial outcomes.

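### The gain-score Cohen's d carries its own significance criterion beside the mixed-model test, with no statement of which decides and no cluster terms described for d

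*Protocol article*

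**What the plan says.** All the wording at issue is in the Protocol article, under Analysis of primary and secondary study outcomes.

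- **Model rule.** "We will run a linear mixed-effects model comparing intervention and control groups on each primary and secondary outcome". The model has crossed random effects for schools and leaders, nesting of observations, participants and groups, and age and sex as covariates. Its interpretation is given as "Significant (*p* < .05) condition × time interactions in predicted directions will indicate that the intervention condition produced more rapid improvements in outcomes", over the window "across the full study period (baseline to 4-week endpoint), as compared to the control".
- **Effect-size rule.** The next paragraph introduces effect sizes for "change in depressive symptoms (the primary study outcome) using differences in means". They are to be calculated "using differences in means; these ESs will compare mean gain scores", "reflecting changes in each outcome from baseline to post-treatment for youths in the Shamiri intervention versus study skills control intervention". It then adds: "Statistically significant, positive Cohen’s *d* values will indicate greater improvements for intervention group youths versus control group youths".

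No alpha, test or standard error is given for d. No sentence ranks the two results, requires both, or calls d descriptive. The section on nesting, missingness and imputation lists four levels of clustering above the repeated measures, and provides for twenty imputations of missing item-level and subject-level data.

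**The concern.** Both sentences take the same form: a significant result will indicate benefit. An effect size needs no significance criterion to do its job. Once one is attached, the plan has a second test of the same outcome.

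The two tests are not described as having the same error term. The interaction comes from a model that carries groups, leaders and schools. The d is a difference in mean gains, with no model or cluster term mentioned. Youths who share a group and a leader may change together. If so, a participant-level test of gains understates the standard error and reaches significance too easily. At stake is a report in which the clustered model is null, d is significant, and the plan's own sentence can be cited for greater improvement on depression.

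**Working it through.** The plan states no error rate for either rule, so there is no figure of its own to reproduce. The sample-size calculation does not bear on this point.

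**Inputs from the Protocol article**
- Assessments at screening, week 2, week 4 and week 6 (Trial design).
- Interaction window from baseline to week 4 (Analysis of primary and secondary study outcomes).
- Target enrolment 420 (Sample size and statistical power).
- About 48 groups (Group leader selection and training), so 420 / 48 = 8.75 youths per group.

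**Assumed, because the document gives none**
- Intraclass correlation (ICC) of change within groups: .02, .05 and .10.
- Linear time, and residual correlation that is compound symmetric or AR(1) at .7 per two weeks.
- A d tested at participant level, at two-sided .05.

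**Step 1: are the two contrasts different on the stated window?** For weeks 0, 2 and 4 the deviations from the mean time are −2, 0 and 2, with sum of squares 8. With complete data the least-squares slope is (−2·y0 + 2·y4) / 8 = (y4 − y0) / 4, which is the gain divided by 4. The contrast is the same, so any difference between the rules comes mainly through the error term. A null simulation (20,000 runs, 48 groups of 9, group-level slope test against participant-level gain test) gave 5.9% two-sided for significance on either rule with no clustering.

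**Step 2: what if d is tested without cluster terms?** The variance of the arm difference is inflated by DE = 1 + (8.75 − 1) × ICC, and the true two-sided error is 2 × [1 − Φ(1.96 / √DE)].

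| ICC | DE | 1.96 / √DE | Two-sided error | Benefit direction (half) |
|---|---|---|---|---|
| .02 | 1.155 | 1.824 | 6.8% | 3.4% |
| .05 | 1.3875 | 1.664 | 9.6% | 4.8% |
| .10 | 1.775 | 1.471 | 14.1% | 7.1% |

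The simulation, on weeks 0, 2 and 4, gave 6.8%, 9.4% and 14.5% for the unclustered gain test. The group-level slope test stayed at 4.6–5.1%. Significance on either rule gave 7.0%, 9.5% and 14.5%, so nearly all of the excess comes from d.

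**Step 3: what if week 6 also enters the slope?** The slope weights are (−3, −1, 1, 3) and the gain weights (−1, 0, 1, 0). Under compound symmetry their correlation is 4 / (√20 × √2) = 0.632; under AR(1) at .7 it is 0.797. From the bivariate normal, the chance that at least one exceeds 1.96 in absolute value is 8.6% and 7.8%. In the benefit direction it is 4.3% and 3.9%, against 2.5% for a single test.

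**The case against.** The best defence is that d has a different role. The mixed model is named as the comparison and given an alpha. The d paragraph opens by announcing effect sizes and gives no test. On that view its last sentence is only a key to the sign, and the standard error of an effect size is detail that an article may leave to a fuller plan.

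Part of this stands. The document nowhere says that either result is enough, and it neither adopts nor excludes a clustered standard error for d. The figures in Step 2 are therefore conditional, not a description of a stated procedure. What does not stand is the sign-key reading: a sign key would not need the words *statistically significant*. The problem is a sentence that the plan contains, not a detail that it leaves out.

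A reader might infer more: that the two rules test materially different things, so that they would often disagree and the trial has two separate chances at significance. The documents do not support that. It needs week 6 in the slope, whereas the interaction is interpreted over baseline to week 4, and imputation largely removes differences due to missing visits. A week-6 assessment is scheduled, and the sample-size section counts five measurement points where Trial design lists four. Step 3 is therefore possible, but it is not the stated window.

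**Conclusion.** The point holds in a limited form. The plan gives d its own significance criterion for depressive symptoms and does not say that the interaction test decides. On the stated window the two results estimate nearly the same quantity, and the exposure is the error term of d. A d tested without cluster terms would have a two-sided error of about 7% to 14% over assumed ICCs of .02 to .10, and a false-benefit rate of about 3.4% to 7.1% against 2.5%. If d were tested with the clustered standard error on weeks 0, 2 and 4, little inflation would remain. The 7.8–8.6% for claiming on either rule applies only if week 6 enters the slope. Because both rules are directional, the two-sided figures overstate false claims of benefit by about a factor of two, although the ratio to nominal is similar or unchanged. The wording should be corrected; it does not invalidate the main analysis.

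**What to change.** In the effect-size paragraph:

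1. Remove statistical significance as a criterion, keeping the statement that positive d favours Shamiri.
2. State that the condition-by-time test in the mixed model alone decides each primary outcome. The paragraph names depression only, while the Background section names both depression and anxiety as primary, so the sentence should cover both.
3. Report d as a descriptive effect size with a confidence interval from the clustered model's standard error.
4. Name the standardising SD in advance. It need not be the baseline SD: participants are selected on baseline PHQ-8 or GAD-7 scores, which can narrow the baseline spread and enlarge d.

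The cost is one or two sentences and no new data, because the model is fitted anyway. The sponsor gives up a second significance statement. Trial status lists the trial as completed, so the clarification would govern reporting. It can be recorded in the registry and repository, as Quality control and trial management already provides for changes to analyses.

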### Quality control and trial management

The management structure comprises of the co-principal investigators (PIs), a research management group, and a data monitoring committee. The research management group is responsible for conducting the trial—including recruiting participating schools and students, obtaining consent, and other study activities—and will meet weekly to discuss trial progress. The PIs will oversee the research management group meetings. The research management group will provide day-to-day on-site support for group leaders and research assistants. The data monitoring committee—which will consist of the PIs who are affiliated with Shamiri Institute and independent members affiliated with the Jomo Kenyatta University of Agriculture and Technology and Kenyatta University—will review safety data as well as oversee the collection and entry of data from the study. Data from the paper questionnaires, which were stored in a locked room in study headquarters, will be double-entered by members of the study-team into a secure and encrypted Excel database. To ensure data quality, processes like double data entry, random data checks, and range check for data values will be adopted under the guidance and supervision of the research management team. Data will be stored in a secure database which will be locked after all the data have been cleaned and entered. During the study, the research management group will collect spontaneous and unsolicited reports of adverse events and other unintended effects of trial interventions or trial conduct. One member of the research team, who is a clinical psychologist, will serve as the point person for any information about adverse events, participant risk, or trial conduct. Upon receiving such information, the PIs will reach out to the MUERC for guidance. Trial conduct will be assessed by the MUERC. Finally, any modifications to the trial protocol (including changes to eligibility criteria, outcomes, and analyses) will be reported to the MUERC, documented in the trial registry, made public in the trial’s Open Science Framework’s repository, and circulated to all relevant parties.

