## Methods

### Study design

#### Trial design

The trial is a randomized controlled trial with two arms: the Shamiri intervention and a study-skills control intervention. The intervention and control conditions are described in detail later and summarized in Table 1. Interventions will be delivered in schools to groups of 10–13 youths by high school graduates trained to be lay-providers. Assessments will be administered at initial screening, 2-week midpoint, 4-week endpoint, and 2-weeks post endpoint. Academic performance data on grades and national exams will be collected for the school-term before, during, and after study participation. Any data required to support the protocol will be publicly available in an online repository [10.17605/OSF.IO/KTW25] or upon request.

**Table 1 Tab1:** Arms of the Shamiri randomized control trial

Study arm	Content	Delivery
Shamiri intervention	Consists of four sessions made up of three modules: growth-mindset (two sessions), gratitude (one session), and virtues (one session).	High school graduates trained as lay-provider (“group leader”). One group leader will be assigned to each group of 10–13 youths.
Study-skills control	Consists of four sessions with content that focus on study skills. Specific modules will include note-taking, effective study strategies, tips for time management, and the study cycle. Equal dose and duration as Shamiri intervention.	High school graduates trained as lay-providers (“group leader”). One group leader will be assigned to each group of 10–13 youths.

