### Procedures

#### Participant recruitment and screening

In all four participating schools, students in Form One, Form Two, and Form Three (and in smaller schools Form Four) will be notified about the study by the school principals and other administrators. All students aged between 13 and 18, inclusive, will be eligible for the study if they self-report either elevated depression symptoms or elevated anxiety symptoms—indexed by a score of 15 or higher on the Patient Health Questionnaire (PHQ)-8 (indicating moderate or severe depression) or a score of 10 or greater on the GAD-7 (indicating moderate or severe anxiety) [27, 28]. No other exclusion criteria will be applied. Of eligible students, approximately 140–180 will be randomly selected at each school to participate in the study. See the “Randomization, treatment allocation, and blinding” section for more information on selection and randomization.

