Students will complete a questionnaire battery to determine study eligibility. To control for ordering effects, scales in the questionnaires will be presented in different orders. Parental consent will be sought for all minor participants. As the schools in which we will be conducting study activities are boarding schools, many of the students will not have direct access to their parents [24, 25]. Additionally, because of the logistical difficulties of the study team obtaining written consent from parents who live in many different parts of the country—many quite distant from the schools and not readily accessible—the Ethics Review Committee at MUERC determined that school principals and other administrators would seek parental/guardian permission from parents of the students interested in the study using their locally available policies and resources—for example, a school in Nairobi county with students from all the geographical counties in Kenya may call or write parents/guardians—per MUERC guidelines. This process was used in the pilot study [13] and has been used in multiple studies with Kenyan adolescents [24, 25, 29]. Only students for which parental permission will be obtained through this process will be allowed to participate in the study. School administrators will then gather these students in classrooms or school halls where they will meet the study team. Here, the study team will further inform them about the study and that their participation is voluntary and that they can opt out. After being provided with an opportunity to ask questions, they will provide informed consent if they wish to participate. Only participants for whom informed consent or informed assent and parental consent (in the case adolescent minors) is received will be allowed to participate. The study team and a school administrator will witness the process of obtaining informed consent. On the consent form, participants will be asked if they agree to the use of their data should they choose to withdraw from the trial. Participants will also be asked for permission for the research team to share relevant data with people from the Universities taking part in the research or from regulatory authorities, where relevant. This trial does not involve collecting biological specimens for storage. There is no anticipated harm for trial participation and there is no provision for post-trial care. See Fig. 1 for a participant flowchart.

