#### Randomization, treatment allocation, and blinding

Following baseline assessment and recruitment, youths who meet the inclusion criteria will be randomly allocated within each school to the Shamiri intervention or the study-skills control condition using a computerized random number generator in R Studio. We will use stratified randomization to ensure consistent baseline characteristics (age, form, and sex if mixed school) across groups. There will be no special criteria for discontinuing or modifying allocated interventions. Participants and group leaders will not be blinded to treatment allocation. However, they will not be informed of study hypotheses. To control for possible contamination, the study will be presented to all eligible students as a Wellness and Academic Functioning Program that was intended to improve both academic functioning and wellness. Both conditions will also be of equal duration and will require similar efforts, and group leaders will be instructed to collect study materials at the end of each session (to prevent students from noticing differences in their program materials and learning from others’ materials during the study).

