The group leader training, which will be conducted by members of the research team, will begin with 4 h of general communication and group leadership skills such as active listening, noting connections between group members, handling conflicts within the groups, and referring students in need to appropriate school officials if necessary. Group leaders will then be trained didactically in the specific content of each week of the interventions. All group leaders will receive detailed and structured outlines of the content of each intervention and control session. The outlines will include sample wording for the group leaders. The last six of the 10 h of training will consist of role-plays in which the leaders practice leading groups in portions of the protocol. Following the role-plays, leaders receive feedback from their fellow group leaders and from the study team. The leaders are then asked in the full group setting to reflect on their experiences and learnings from the role-plays. A detailed protocol for the recruitment and training of group leaders is available elsewhere [30].

Upon completion of training, group leaders will be randomly assigned to lead either Shamiri intervention or control groups. Given that we will have about 48 groups of up to 15 youths in the entire study, group leaders will be randomly assigned to either the intervention or control condition at each school. That is, the randomization process will be repeated for each distinct school. For instance, one group leader might lead a study-skills control group in School A but a Shamiri intervention group in School B. This randomization should allow us to account for group leader differences in competence and leadership style. However, group leaders will be instructed to strictly follow the protocol manual for the condition that they will be leading and not use content from the other condition during their sessions. Student composition in the groups will reflect the composition of the school. In a single-sex school, all groups will be single-sex.

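### Harms are collected only by spontaneous, unsolicited reports, which are likely to miss symptom worsening that the PHQ-8 and GAD-7 scores already record

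*Protocol article*

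**What the plan says.** On harm collection, Quality control and trial management states: "During the study, the research management group will collect spontaneous and unsolicited reports of adverse events and other unintended effects". The other safety steps in that section act on information once it exists. A clinical psychologist on the team "will serve as the point person for any information about adverse events, participant risk, or trial conduct", the principal investigators then turn to the ethics committee for guidance, and the data monitoring committee "will review safety data as well as oversee the collection and entry of data from the study". No further source of safety data is named.

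Group leader training includes "referring students in need to appropriate school officials if necessary". That is a route to care, and the article states no link from it to the trial's harm record.

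Students aged 13 to 18 enter "if they self-report either elevated depression symptoms or elevated anxiety symptoms", with cut-offs of PHQ-8 of 15 or more, or GAD-7 of 10 or more. On blinding: "Participants and group leaders will not be blinded to treatment allocation". On risk, the recruitment section says: "There is no anticipated harm for trial participation". On the schedule of scores: "Assessments will be administered at initial screening, 2-week midpoint, 4-week endpoint, and 2-weeks post endpoint".

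Analysis of primary and secondary study outcomes tests the condition by time interaction in a mixed model and reports a standardised difference in mean gain. It counts nobody as worsened.

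**The concern.** In a group selected for high symptoms, getting worse is the most relevant harm. A purely passive system records it only if someone volunteers it. The article gives its own reasons to expect silence:

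- Background and Discussion describe stigma that limits help-seeking.
- Group leader selection and training describes cultural norms under which youths mainly listen when adults are present.
- Discussion says that depression and anxiety are not talked about directly in the groups and that the programme is not presented as treatment for them.

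A youth who deteriorates therefore has little prompt to say so. The risk is that few or no reports are taken to confirm that no harm was expected, although the trial holds scores that could examine this.

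**Working it through.** The article gives no figure on harm rates or reporting, so there is none to reproduce. Everything below is illustration.

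**Inputs from the article.** Planned enrolment is 420, taken as 210 per arm (1:1 is assumed). About 48 groups gives a mean size of 420/48 = 8.75; Trial design states 10–13. Up to 10% may discontinue, which leaves 210 × 0.9 = 189 per arm.

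**Assumed inputs.** True worsening of 5%, 10% or 20%; 5%, 10% or 20% of worsenings volunteered; intraclass correlation (ICC) of 0.05 or 0.10 within groups.

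**1. What spontaneous reports would yield.** Expected reports per arm = 210 × worsening rate × fraction volunteered. With 10% worsening (21 youths) and a Poisson chance of none:

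| Fraction volunteered | Expected reports | Chance of none in an arm |
|---|---|---|
| 5% | 21 × 0.05 = 1.05 | exp(−1.05) = 35% |
| 10% | 21 × 0.10 = 2.1 | exp(−2.1) = 12% |
| 20% | 21 × 0.20 = 4.2 | exp(−4.2) = 1.5% |

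**2. What a handful of reports can tell.** If worsening doubles (21 v 42) and 10% is volunteered in both arms, 2.1 v 4.2 reports are expected. Equal worsening (21 v 21) with 10% v 20% volunteered gives the same 2.1 v 4.2. For 2 v 4 reports the risk ratio is 2, with SE(log) = sqrt(1/4 − 1/210 + 1/2 − 1/210) = 0.86 and 95% CI 0.37 to 10.8.

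**3. Why mean change does not fill the gap.** A constructed example: in arm A 20% rise by 5 points and 80% fall by 5, so the mean change is 0.2 × 5 − 0.8 × 5 = −3. In arm B 10% rise by 5 and 90% stay level, so the mean is +0.5. The mean favours arm A, which has twice the deterioration.

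**4. What the scores could show.** For 42/210 v 21/210 the difference is 10 points, SE = sqrt((0.1 × 0.9 + 0.2 × 0.8)/210) = 3.45 points, 95% CI 3.2 to 16.8. With a design effect of 1 + (8.75 − 1) × 0.05 = 1.3875 it is 2.0 to 18.0. This assumes error-free classification, which is too kind. Suppose 80% sensitivity and 10% false positives:

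- 10% becomes 0.8 × 0.10 + 0.1 × 0.90 = 17%.
- 20% becomes 0.8 × 0.20 + 0.1 × 0.80 = 24%.
- The difference is 7 points, SE = sqrt((0.17 × 0.83 + 0.24 × 0.76)/210) = 3.92, 95% CI −0.7 to 14.7, before clustering or loss.

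**5. Precision of the proposed table.** Half-width = 1.96 × sqrt(2p(1 − p)/n × design effect), in percentage points:

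| Setting | p = 5% | p = 10% | p = 20% |
|---|---|---|---|
| n = 210, no clustering | 4.2 | 5.7 | 7.7 |
| n = 210, ICC 0.05, size 8.75 (1.3875) | 4.9 | 6.8 | 9.0 |
| n = 210, ICC 0.05, size 13 (1 + 12 × 0.05 = 1.6) | 5.3 | 7.3 | 9.7 |
| n = 210, ICC 0.10, size 8.75 (1.775) | 5.6 | 7.6 | 10.2 |
| n = 189, ICC 0.05, size 8.75 (1.3875) | 5.2 | 7.1 | 9.5 |

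Clustering by group leader would widen these further.

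**The case against.** The strongest reply is that the protocol plans no comparison of adverse events between arms. Reports go to a psychologist and the ethics committee to protect participants, and the statement on anticipated harm is a risk statement in the recruitment and consent text, not a hypothesis. Moreover, symptoms are the primary outcome, so a net excess of worsening would appear there, and an extra table is something an article may leave to an analysis plan. Much of this stands. What remains is that the article positively states a passive method, and that a mean can conceal a worsening minority (step 3).

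A reader might infer that unblinded allocation biases harm reports by arm. The documents do not support that as a finding. Hypotheses are withheld, both arms share one programme label, duration and effort are matched, and leaders are re-randomised to condition at each school, which tends to balance leaders' own readiness to report. The twofold reporting difference in step 2 is an assumption. It shows only that a few reports could not separate the two explanations.

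It is also fair to say that the PHQ-8 and GAD-7 are self-reported by the same unblinded youths, and that setting 10% capture against perfect classification flatters the scores. The misclassification example in step 4 concedes this. The advantage of the scores is that every participant is asked, on the same schedule in both arms.

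**Conclusion.** The point holds in a limited form. Spontaneous, unsolicited reporting is the only harm-collection method stated. In this population and setting it is likely to miss symptom worsening, and the planned mean-change analyses do not count it. How much would be missed cannot be known from the article. Under the assumed rates, an arm with 21 worsened youths would produce between about 1 and 4 reports.

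A reader might go further and conclude that safety oversight is absent or that the trial result is compromised. Neither follows: a point person, ethics committee contact and a monitoring committee are all described, and the primary efficacy inference is unaffected. Biased reporting by arm remains a possibility only. This is a cheap improvement of the lowest severity.

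**What to change.** Keep spontaneous reporting and add one descriptive safety table from existing scores. By arm, at midpoint, endpoint and 2-week follow-up, give:

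- the number and proportion whose PHQ-8 or GAD-7 total rose from baseline by at least a fixed amount. Five points is an example and an assumed value; set it before looking at scores by arm, with a second threshold as a sensitivity check;
- the number with missing scores, using observed values;
- the arm difference with a 95% confidence interval that allows for clustering.

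Report it beside the adverse events. New crossing of PHQ-8 of 15 or GAD-7 of 10 is optional. It applies only to those below that cut-off at baseline, that is, those who qualified on the other scale alone, so show that denominator. The half-widths above do not apply to it.

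Trial status gives the trial as completed, so label the table post hoc for this cohort and pre-specify it in any re-use of the protocol. Care of individual participants stays with the investigators and the ethics committee.

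The cost is a sentence and a table, with no new measure, visit or staff. The downside is that the scores are unblinded self-report and some rises are measurement noise, so the arm comparison matters more than the raw count, and only a large excess would be visible.
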